5.3 SCREENING EXAMINATIONS

5.3.1 Conditions for examination are discribed in section 5.2.2.

5.3.2 Content of first screening examination.

This examination will include an OGTT and the following measurements

(1) Height (to the nearest cm without shoes).

(2) Weight (to nearest 0.1 kg in light indoor clothes, without shoes).

5.3.3 Content of second screening examination.

This examination will include an OGTT. Previous diagnoses or treatment for diabetes, IGT, or gestational diabetes will be sought. If present then the patient is ineligible for inclusion in the trial (see 5.1.2). Treatment for hypertension, hyperlipidemia, other serious illnesses and use of medicines, alcohol and tobacco will be recorded. The following measurements are made

(3) Measurement of waist and hip circumferences.

(4) Measurement of sagittal and transverse diameters.

(5) 12-lead supine resting ECG (to be forwarded to the ECG Reading Center).

5.3.3 Content of enrollment examination. This examination will include a medical history and physical examination by a physician.

The following core data will be obtained and recorded:

(6) Blood pressure measured with a mercury sphygmomanometer (1st and 5th phase).

(7) Fasting venous blood specimens for serum total and HDL cholesterol, serum triglycerides, serum creatinine, liver function tests (serum bilirubin, alkaline phosphatase, albumin, and ALT or AST), thyroid stimulating hormone, HbA1c by HPLC, and an extra 10 ml of serum to save frozen.

(8) HLA-typing and storage of DNA samples for genetic markers.

(9) WHO cardiovascular questionnaire will be completed.

(10) Subjects will be asked to complete a dietary diary.

(11) Physical activity (occupational and leisure) will be assessed by questionnaire.

(12) Assessment of physical fitness by walking test.

(13) B-mode ultrasound imaging of carotic arteries.

(15) Lean body mass using Futrex infrared equipment.

(16) Hemostatic factors: The activity of the hemostatic system, and its contribution to the progression and complications of atherosclerosis will be assessed by measuring fibrinogen, F VII:C, prothrombin fragment F1+2 and PAI-1 activity both **in the beginning and at the end of the study**.

5.4 ANNUAL EXAMINATIONS

5.4.1 Conditions for examination. Any acute intercurrent illness or injury should be resolved before the examination is carried out. The annual examination will be undertaken at each anniversary of randomization.

5.4.2 Content of annual examinations. The examination will include an OGTT and a medical history and physical examination by a physician. If the OGTT is diabetic, it is repeated after 1 week. If also the second OGTT is diabetic, the subject has reached the study endpoint.

(1) Any alteration in health status since the previous annual examination will be recorded. If a diagnosis of myocardial infarction, angina or diabetes has been made in the preceding year, then a copy of the clinical case notes must be forwarded to the Endpoints Committee.

(2) Treatment for hypertension, hyperlipidemia, other serious illnesses and use of medicines, alcohol and tobacco will be recorded.

(3) All of the core data described under the screening and enrollment examinations will be collected annually (excluding ultrasound measurements and genetic markers).

(4) B-mode ultrasound imaging of carotic arteries will be repeated at the last visit.

5.5 POST-STUDY FOLLOW-UP

All active treatments will cease at the end of 6 years (for those randomized in the first year of the study) or 5 years (for those randomized in the second year). The treatment will conclude with the usual annual examination (including an OGTT, Section 5.4). Thereafter, the reinforcement for the intensive diet-exercise program will be discontinued, although the patients assigned to this treatment will not be discouraged from continuing it on their own. All subjects who have not already reached the diabetes endpoint will be retested by OGTT three months and six months after termination of treatment. If one of these OGGTs indicates diabetes, the test will be repeated for confirmation of the diagnosis as described in Section 6.4.2. Following the six month OGTT, all procedures as specified by this protocol terminate, and further advice to subjects will depend on the outcome of the study.

CHAPTER 6. TREATMENT AND TESTING PROCEDURES

6.1 DIET-EXERCISE TREATMENT

Combined diet-exercise treatment will be compared to standard diet-exercise group. The groups will differ in several respects, including diet, physical activity, and weight loss.  Their comparison is intended to provide evidence as to which compo­nents affect the endpoint, but the main question is whether the combined treatment regimen is effective.

6.1.1 Standard diet-exercise treatment group. Subjects will be advised at entry to the trial by the dietitian to consume a diet with <30% of calories derived from fat, and to reduce alcohol and tobacco consumption to whatever extent possible.  Subjects should be advised to consume at least 15% of the daily calories at breakfast (defined as a meal taken within two hours of arising). Subjects will be advised to adjust total calories with the goal of weight loss to achieve body mass index <25 kg/m2.

These dietary goals will be implemented only by verbal or written instructions from a dietitian at the enrollment and annual visits.  None of the additional measures described below will be used.

6.1.2 Special diet-exercise treatment group.

(1) Subjects will be advised by the dietitian to consume a diet with 50% of calories derived from carbohydrate, 30-35% from fat (10 E% saturated fat, 20 E% unsaturated fat), cholesterol <300 mg/day, and 0.8 g protein/kg body weight/day. Dietary fiber will be increased to 30 g/day, or more if tolerated. This goal may be achieved through use of natural high fiber foods and by supplementation by soluble fibers such as beet fiber (Hagander, et al, 1988b). The caloric content of any supplemental fibers will be taken into account in the total caloric content of the diet. If subjects do not tolerate this much dietary fiber, the amount should be reduced to a tolerable level rather than withdrawing the subject from the diet treatment. Subjects will be advised to consume at least 10% of the daily calories at breakfast. Subjects will be encouraged to reduce alcohol and tobacco consumption.

(2) Intensive weight loss advice should be provided aiming to reduce body mass index to <25 kg/m2. If the subject does not succeed to lose weight during the first 6 months of the study and if his body mass index is >30, then VLCD (very low calorie diet) treatment may be used.

(3) Subjects will receive frequent regular dietary advice (see Table 4.1 for scheduled visits to the dietitian).

(4) Subjects will be advised to increase their level of physical activity by engaging in a walking program and will be given other advice on increasing leisure activities aiming at increasing the lean body mass and aerobic capasity.

(5) Frequent group meetings including diet and exercise activity and also aiming at improving the compliance will be held regularly throughout the study period.

6.2 MONITORING FOR COMPLIANCE AND ENDPOINTS

6.2.1 Interim visits. Interim monitoring will be for the primary purposes of improving compliance with the diet-exercise therapy. Interim visits will take place at 1, 2, and 3 months after randomization and thereafter every three months for the duration of the study. When this schedule coin­cides with the annual examinations (i.e. at months 12, 24, 36, 48, 60, and 72), the interim and annual examinations will be combined into a single visit.

At the interim visits, subjects will be seen by a dietitian or nurse for assessment of general health and measurement of body weight. No physical examination or laboratory tests will be performed unless a physician considers this to be indicated. Dietary, exercise, and weight loss counseling will be provided according to the assigned diet-exercise treatment.

The interim visits can be conducted in usual medical clinics, community centers, or patients' homes, as needed to ensure compliance.

6.2.2 Annual examination and OGTT.  The primary end point (diabetes) will be assessed annually as described under the Annual Examination (Section 5.4). The results of the OGTT at the annual exam should be interpreted as follows:

1. If the results are normal or indicate IGT (i.e. fasting plasma glucose <7.8 mM (<140 mg/dl) and 2hr plasma glucose <11.1 mM (<200 mg/dl), then continue the assigned treatments.

2. If the results are diagnostic of diabetes (i.e. fasting plasma glucose >7.8 mM (>140 mg/dl) or 2hr plasma glucose >11.1 mM (>200 mg/dl), then repeat the OGTT after one week. If the repeat test results are normal or indicate IGT, then resume the assigned treatments.  If they are diagnostic of diabetes, the subject has reached the study endpoint.

If at any time other than an annual evaluation the physician suspects, on the basis of signs or symptoms, that diabetes has developed in a patient, the patient should be evaluated as follows. If his/her condition permits, a fasting plasma glucose should be measured. If it meets the diagnostic criterion for diabetes (plasma glucose >7.8 mM (>140 mg/dl) and the patient's condition allows further testing, he/she should be evaluated as described for annual evaluations (i.e., an OGTT while continuing treatment, and if it is diagnostic of diabetes, a repeat test after seven days). If the patient's condition is urgent, a diagnosis of diabetes can be made by symptoms of diabetes and repeated fasting or casual plasma glucose concentrations >11.1 mM (>200 mg/dl). In this case, a standard OGTT as described under annual evaluations should be performed when and if the patient's condition improves sufficiently after standard treatment for diabetes and the fasting plasma glucose is <11.1 mM. If the fasting plasma glucose remains >11.1 mM after stabilization, no further OGTT is required. When the diagnosis of diabetes is confirmed, the subject has reached the study endpoint.

6.2.3 Diet-exercise treatment. Compliance with the diet-exercise program will be monitored by interviews with subjects by the dietitian at each clinic visit.

6.2.4. Physical activity assessment. The assessment of physical activity and cardiorespiratory fitness will be carried out using four different methods: (a) a questionnaire on 12-month leisure time physical activity history (Salonen and Lakka 1987, Lakka and Salonen 1992) (b) 24-hour total physical activity recording (Salonen and Lakka 1987, Lakka and Salonen 1992) (c) a 2-km walking test for assessing cardiorespiratory fitness as proposed recently (Kline et al 1987, Oja et al 1991). (d) assessment of maximal oxygen uptake form heart response to a given submaximal workload using a bicycle ergometer recorded at steady-state with a heart rate > 120 beats/min.

The measurements will be done before the randomization and on every annual visit. The walking test will also serve as an assessment of qualification of study subjects to the intervention program. If a person fails to complete the walking test he/she will not be recruited to the study.

Leisure time physical activity (LTPA) will be assessed by a 12-month leisure time physical activity history (Salonen and Lakka 1987, Lakka and Salonen 1992), modified from the Minnesota leisure time physical activity questionnaire. (Taylor et al 1978) The checklist in the 12-month history include the most common leisure time physical activities of middle-aged Finnish men, selected on the basis of a previous population study in Finland. (Mälkiä et al 1988) Leisure time physical activities are classified as conditioning and nonconditioning physical activity and walking and bicycling to and from work. Main categories of conditioning physical activity are 1. walking, 2. jogging, 3. skiing, 4. bicycling, 5. swimming, 6. rowing, 7. ball games, and 8. gymnastics, dancing, or weight lifting. Main categories of nonconditioning physical activity are 1. crafts, repairs, or building, 2. yard works, gardening, farming, or snow showeling, 3. hunting, picking-up berries, or cathering mushrooms, 4. fishing, and 5. forest work or forestry. Walking and bicycling to and from work will be asked separately because these physical activities are common in Finland and they are generally less intensive than conditioning walking and bicycling.

In the 12-month history the subjects are asked to fill in the frequency (sessions/each month), the average duration (hours and minutes/session), and the intensity (scored 0=recreational, 1=conditioning, 2=brisk conditioning, and 3=competitive, strenuous exercise) of each physical activity performed during the previous 12 months. Missing data are completed by a trained interviewer. Each intensity class of each physical activity has its own metabolic unit (MET) value, which represents the intensity of the physical activity. The MET is the ratio of metabolic rate during physical activity to the metabolic rate at rest. One MET is approximately 1 kcal/kg/hour and corresponds an oxygen uptake of 3.5 ml/kg/minute. The MET-values for specific physical activities were revised on the basis of a synthesis of available empirical data. (Durnin and Passmore 1967, Fox et al 1972, Mälkiä et al 1988) The total duration of each physical activity is computed by multiplying the frequency and the average duration and the energy expenditure by multipying the total duration and the intensity by body weight in kilograms.

Total physical activity will be assessed by a 24-hour total physical activity recording. (Salonen and Lakka 1987, Lakka and Salonen 1992) Physical activities are classified according to their intensity, as expressed in METs, into eight groups. The subjects record the physical activities in periods of 30 minutes and total time spent in each physical activity during 24 hours is summed. Energy expenditure in each physical activity during 24 hours is computed by multiplying the duration and intensity of the physical activity by body weight in kilograms. Total energy expenditure in physical activity is computed by summing energy expenditure values of individual physical activities.

6.2.5 Assessment of diet. The assessment of diet will be carried out using a 3-day food diary. The members of the intervention group will keep food diary every three months; the members of control group annually.

CHAPTER 7. END-POINTS CLASSIFICATION

The primary end point for the trial is worsening from IGT to diabetes mellitus.

The secondary end points for the trial are:

(1) Definite myocardial infarction (fatal and non-fatal) and sudden cardiac death

(2) Angina

(3) Possible myocardial infarction

(4) Intermittent claudication

(5) Stroke.

(6) Atherosclerosis

7.1 WORSENING FROM IGT TO DIABETES

This will be defined by the results of an oral glucose tolerance test which is diagnostic of diabetes (i.e. fasting plasma glucose > 7.8 mM or 2 hr plasma glucose > 11.1 mM). Confirmation by a repeat OGTT after seven more days is required, as described in Section 6.4.2.

7.2 CARDIOVASCULAR END POINTS

7.2.1 Definite myocardial infarction:

(1) a definite ECG abnormality, or

(2) typical or atypical symptoms and cardiac enzymes that are elevated to more than twice the normal, or

(3) typical symptoms together with abnormal enzymes with an absent or non-codable ECG.

(4) fatal cases, whether sudden or not, with naked eye appearance of fresh myocardial infarction and/or recent coronary occlusion found at necropsy (ante-mortem thrombus, hemorrhage into an atheromatous plaque or embolism).

7.2.2 Possible myocardial infarction: Typical symptoms without ECG changes or enzymes results that place them in the category definite myocardial infarction.

7.2.3 Ischemic cardiac arrest: Patients who were successfully resuscitated from a cardiac arrest but did not meet criteria for myocardial infarction.

7.2.4 Sudden cardiac death: Coronary heart disease stated on the death certificate and death known to have occurred within one hour after the onset of symptoms.

7.2.5 Unwitnessed cardiac death: Coronary heart disease stated on the death certificate with no evidence to justify a classification of sudden cardiac death.

7.2.6 Angina: Defined by a positive response to the WHO Questionnaire.

7.2.7 Intermittent claudication: Defined by a positive response to the WHO Questionnaire.

7.2.8 Stroke: Fatal stroke is defined by the End Points Committee after a review of all the available clinical documentation for subjects with a death certificate ICD code - (9th Revision). Documentation will be reviewed without knowledge of the subject's treatment. Non-fatal stroke is defined by a clinical diagnoses confirmed by the End Points Committee after review of all available clinical documentation.

7.2.9 Atherosclerosis: In addition to the "core" data mentioned above, measurements of the wall thickness (intima+media) of the carotid arteries will be performed at the first run-in examination using a non-invasive B-mode ultrasound technique. The measurements will be performed under rigorous standardization and quality control. The measurements in different centers will be recorded on video cassettes, which will be read centrally. The reading center will be blinded as to the treatment group of the participant. Ultrasound measurements of the distensibility of carotid arteries are also considered depending on the avaialability of suitable equipment and necesaary expertice. These measurements will be repeated at the end of study period (6th year) in order to get a quantitative assessment of the progression of atherosclerosis in different treatment groups.

7.3 END-POINT CLASSIFICATION

Minnesota coding will be performed by the ECG Reading Center. The End Points Committee will evaluate the classification of all end points with the exception of angina and intermittent claudication which will be determined by the response to the WHO Questionnaire. The committee will also review the documentation of diabetes diagnoses to confirm that this endpoint has been defined according to protocol. All end point classifications will be made without knowledge of the subject's treatment. Classification will not be altered once the treatment codes are broken.

CHAPTER 8. DATA ANALYSIS

8.1 INTRODUCTION

Data analysis in the DPS will be designed to meet the study's scientific objectives, recapitulated here:

1. To assess the efficacy of a diet-exercise program

in preventing or delaying the development of type 2 diabetes in persons with IGT.

2. To study the clinical course and prognosis of IGT.

3. To assess efficacy of the program in preventing atherosclerosis

The data developed in the DPS will provide a foundation for information not only on the treatment, but also on the natural history and prognosis of IGT with particular respect to the development of overt diabetes and macrovascular disease.

Presentations of DPS results will include the numbers of subjects on which the results are based as well as measures of sampling variability, such as standard errors or confidence intervals.

In addition to analyses directed at meeting the study's scientific objectives, there will also be analyses directed at monitoring data quality and the smooth and efficient operation of the study itself, such as analyses, by Clinical Center, to monitor progress in screening and subject enrollment, the completeness and internal consistency of data submitted to the Coordinating Center, delays in the submission of the data, and missed visits and study dropouts.

8.2 PRETREATMENT CHARACTERISTICS

An analysis of pretreatment characteristics of enrolled subjects, by Clinical Center and by assigned treatment, will be undertaken in order to provide descriptions of the population studied and to determine whether stratified randomization succeeded in balancing the various treatment groups with respect to potential risk factors for diabetes. In the unlikely event that such balance is not achieved, methods of covariate adjustment, such as standardization of rates or the Cox proportional hazards model will be used.

The pretreatment characteristics to be analyzed include:

o age, sex, ethnicity

o physical fitness

o physical activity

o waist and hip circumference, waist-hip ratio

o sagittal and transverse diameters

o height, weight, body mass index

o lean body mass

o systolic and diastolic blood pressure, hypertension

o cigarette smoking

o dietary intake

o laboratory measurements (plasma glucose and lipids, serum creatinine, c-peptide, and insulin)

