2.2.2 Diagnosis of IGT and prediction of diabetes. IGT is quantitatively a major problem.  The prevalence increases with age, and, by WHO criteria, reaches 23% at ages 65‑74 years in the U.S. population according to the National Health and Nutritional Examination Survey (Harris, et al, 1987). Several population studies have shown people with IGT to be at increased risk of developing diabetes, although if their glucose tolerance does not deteriorate, they are not at risk of diabetic complications.  There is, however, evidence that they are at increased risk of coronary disease (Fuller, et al, 1980).  There have been at least eleven studies of the rate at which persons with IGT progress to overt diabetes. These studies, summarized in Table 2.1, are difficult to compare because different diagnostic criteria for IGT and diabetes have been used, differing especially for IGT. Most of these predated the WHO criteria (World Health Organization, 1985) for glucose tolerance and used criteria which are much less stringent, i.e. they included many subjects who would be normal by WHO criteria. Thus in those studies using WHO criteria, such as the studies in Malmöhus County (in a subset of subjects meeting WHO criteria for IGT), Nauru, Malmö, Malta, San Antonio, and the Pima Indian study, the incidence rates of diabetes were higher, at 19-61% in 5-10 years. In the others, the two-hour blood glucose at entry was consistently a strong predictor of future diabetes, so it is reasonable to estimate that had the more stringent WHO criteria been used, the incidence rates might have been higher and similar to those in the studies in which WHO criteria were used. The best estimates of incidence rates to be anticipated in subjects with IGT by WHO criteria are based on those studies shown in Table 2.1 in which WHO criteria were used.

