3.5 REGISTRATION, RANDOMIZATION, AND STRATIFICATION

3.5.1 Treatment assignment and registration. Assignment will be issued by the Clinical Center which will register enrollment of subjects upon verification that all eligibility criteria have been met.

3.5.2 Randomization to treatment. Subjects will be randomly allocated to special or standard diet-exercise program in the following way:

Group 1: Special diet - exercise

Group 2: Standard diet - exercise

3.5.3 Stratification. Randomization will be stratified by 1) Clinical Center and 2) the 2-hour post-load glucose obtained during the OGTT:

o Stratum 1: venous plasma glucose = 7.8-9.4 mM (140-169 mg/dl)

o Stratum 2: venous plasma glucose = 9.5-11.0 mM (170-199 mg/dl)

3.5.4 Registration. Subjects are enrolled in the DPS as soon as they are registered by the Clinical Center. The Clinical Center will promptly register a subject upon verification that all eligibility criteria have been met. A registration number (and treatment assignment) is given to the subject according to the randomization list.

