3.8 SAMPLE SIZE AND ENROLLMENT GOAL

We begin sample size determination by estimating the 5-year incidence of diabetes in the untreated persons with IGT to be 28% (see Chapter 2). Because of the uncertainty in the data needed to make this estimate, this figure may be an underestimate of the incidence of diabetes. If so, the power of the study would be greater than the following computations indicate. We are designing the study to be large enough to be able to detect, with 80% power (beta = 20%) at the 2-tailed 5% significance level (alpha = 5%), a 30% reduction in diabetes incidence due to diet-exercise treatment, ie, a reduction from 28% to 19.6%.

The possibility of a reduction in diabetes incidence by at least 30% is suggested by the results of the Malmöhus study (Sartor, et al, 1980) analyzed in accordance with randomized treatment assignment and by the nonrandomized treatment study of Eriksson and Lindgärde (1991). We are assuming that noncompliance in the DPS will be no worse than in these previous studies; therefore we are making no further adjustment for noncompliance. We will, however incorporate an adjustment for losses to follow-up, including deaths.

Letting p1 and p2 denote, respectively, the proportion of events (incidence of diabetes) in the control and treated groups, respectively, then, according to Halperin, et al (1968), the sample size required in each of the two groups is

N = {Zα[2p(1 - p)]1/2 + Zß[p1(1 - p1) + p2(1 - p2)]1/2}2 / [p1 -p2]2,

where p = (p1 + p2)/2 and Zα and Zß are the normal deviates associated with α and ß. With p1 = .28, p2 = .175, α (2-tailed) = .05, and ß = .20, the total minimum required sample size becomes

2N = 500.

In Malmöhus County from 1962-87, the mortality rate among persons aged 45-64 with IGT by WHO criteria was 19/1000 persons per year (Knowler, et al, in preparation), yielding an estimated 5.5-year cumulatie mortality rate of 10% in study participants. Allowing for 10% losses to follow-up from deaths over a 5.5-year period increases the sample size to

2N = 500/(1 - .10) = 556, or approximately 560.

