8.3 OUTCOME VARIABLES

8.3.1 Events. The primary outcome variable is the incidence of diabetes. Other events of interest are defined in Chapter 7. The cumulative incidence of events, by treatment group and, to evaluate prognostic factors, by subgroups determined by pre-randomization characteristics such as those listed in Section 5.3.2, will be analyzed in 1-year follow-up intervals by the lifetable method.

8.3.2 Continuous variables. Mean changes in the following variables, by treatment group and subgroups defined by pre-randomization characteristics, will be analyzed in 1-year follow-up intervals:

o systolic and diastolic blood pressure

o waist-hip ratio; waist and hip circumference

o sagittal and transverse diameters

o body mass index

o lean body mass

o GTT

o serum cholesterol

o serum triglycerides

o serum creatinine

o plasma glucose

o plasma insulin

o serum c-peptide

o glycosylated hemoglobin

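### Section 8.2 makes covariate adjustment depend on observed baseline imbalance, which would normally leave the randomization strata out of the primary comparison

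*Protocol*

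**What the plan says.** Section 8.2 plans a comparison of baseline characteristics by Clinical Center and by arm, partly to judge whether the stratified randomization worked. It continues: "In the unlikely event that such balance is not achieved, methods of covariate adjustment" come into play. Two methods are offered as examples, standardized rates and a Cox model. It does not say what counts as failed balance or which variables would be adjusted for. The list of characteristics runs to about 24 items if each named measurement is counted once.

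Section 3.5.3 says: "Randomization will be stratified by 1) Clinical Center and 2) the 2-hour post-load glucose obtained during the OGTT", with glucose split into 7.8-9.4 and 9.5-11.0 mM. On the second factor, section 2.2.2 reports that "the two-hour blood glucose at entry was consistently a strong predictor of future diabetes". Section 2.3.1 lists the degree of hyperglycemia among the major risk factors for type 2 diabetes in people who already have IGT.

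Section 8.3.1 states: "The primary outcome variable is the incidence of diabetes". Cumulative incidence by treatment group "will be analyzed in 1-year follow-up intervals by the lifetable method". No between-group test is named, and the randomization strata are neither included nor excluded. Section 8.3.2 covers the continuous variables: "Mean changes in the following variables, by treatment group and subgroups defined by pre-randomization characteristics" are analysed in 1-year intervals, with no word on the baseline value.

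**The concern.** This is a rule that the protocol states, not a detail left for later. Whether to adjust, for what and by which method are all settled after the baseline data have been seen by arm. Standardized rates and a Cox model estimate different quantities, so even an agreed imbalance does not lead to one answer.

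The rule also works against the variables with the best claim to inclusion. Clinical Center and 2-hour glucose are the factors that the randomization is built to balance, so they are the least likely to trigger adjustment. In the expected case, section 8.2 therefore points to a primary comparison without them. The balance that stratification buys then reduces the true variance of the treatment difference, but the test's standard error does not reflect it. What is at stake is a little power and a primary result that is not fixed in advance.

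**Working it through.** **The plan's own figure.** Section 3.8 uses an unstratified two-proportion formula. With p1 = 0.28, p2 = 0.175 and p = 0.2275:

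- 1.96 × √(2 × 0.2275 × 0.7725) = 1.162
- 0.8416 × √(0.28 × 0.72 + 0.175 × 0.825) = 0.495
- N = (1.162 + 0.495)² / 0.105² = 249.05, so 250 per group and 2N = 500
- 500 / 0.90 = 556

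Both stated figures reproduce. The wording of 3.8 gives 19.6% rather than 17.5% for the treated group. That is a separate conflict, so both values are used below.

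**How often would the trigger fire?** The protocol sets no threshold. Assume each variable is tested at 5% and the variables are independent. P(at least one imbalance) = 1 − 0.95^k:

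- k = 5: 23%
- k = 10: 40%
- k = 24: 71%

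Many listed variables are correlated (weight, body mass index, waist), so 71% is too high. Even five independent variables make the event far from rare.

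**Effect of omitting the strata: hand check.** The documents give no risks by stratum, so these are assumptions centred on the 28% planning rate. When the strata are balanced by design, the true variance reflects only within-stratum variation, while the unstratified test uses the total, 0.28 × 0.72 = 0.2016.

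- Equal strata, risks 18% and 38% (ratio 2.1): within-stratum variance 0.1916, ratio 0.950. The effective critical value is 1.96 / √0.950 = 2.01, so type I error is about 4.4%.
- Equal strata, risks 12% and 44% (ratio 3.7): within-stratum variance 0.1760, ratio 0.873. The critical value is 2.10, so type I error is about 3.6%.

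A simulation of 200,000 trials (126 per stratum and arm) gave 4.4% and 3.7%. Power for a 30% reduction was 60.4% unstratified against 62.0% stratified in the first case, and 60.6% against 64.8% in the second.

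**Effect of omitting the strata: second simulation.** Assumptions: 500 subjects, five centers with modest differences (log-odds SD 0.3), 40% in the high stratum, blocks of four, 4,000 to 6,000 runs. The table shows the unstratified two-proportion test / Cochran-Mantel-Haenszel test, in percent.

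| Risk ratio, high to low stratum | Type I error | Power, 28% to 17.5% | Power, 28% to 19.6% |
|---|---|---|---|
| 1.0 | 4.5 / 4.7 | 81.4 / 81.7 | 60.3 / 60.8 |
| 1.5 | 5.1 / 5.3 | 81.3 / 82.0 | 61.3 / 62.1 |
| 2.0 | 4.1 / 4.7 | 82.0 / 82.9 | 61.1 / 63.4 |
| 3.0 | 3.7 / 5.1 | 81.6 / 84.0 | 60.9 / 64.6 |

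With 6,000 runs, the simulation standard error of a 5% rate is √(0.05 × 0.95 / 6,000), about 0.3 points. Differences in the first two rows are within noise.

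**Effect of the trigger on type I error.** Simulation with 500 subjects, 5, 10 or 20 baseline covariates (three of them prognostic), 8,000 runs each:

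- Always unadjusted: 4.8-5.1%
- Always adjusted: 4.7-5.0%
- Adjusting only for variables found imbalanced: 4.7-4.8%
- Reporting the most favourable of the three: 6.4-6.8%

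**The case against.** The strongest reply is that most of this rests on silence. A reader might infer that the primary comparison ignores the randomization strata. Section 8.3.1 does not say so: it names no test, and an analysis plan not shown here could stratify. That stands as far as 8.3.1 goes. It does not rescue 8.2, which allows adjustment only on failed balance, so a later plan that always stratified would have to depart from it.

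A reader might also infer that the rule inflates type I error. As written it does not: applied mechanically it holds about 4.7%. The 6.4-6.8% needs an analyst who picks the best result. Section 8.2 does not invite that, but it fixes nothing that would prevent it.

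The statement on 2-hour glucose in 2.2.2 concerns studies that did not use WHO criteria and often covered wider glucose ranges, so it does not show how strongly the two strata within 7.8-11.0 mM differ. That is fair. However, section 2.3.1 names the degree of hyperglycemia as a major risk factor among people with IGT. The direction is supported; the size is assumed.

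Nor is the trial's test shown to be conservative overall. Section 5.1.2 lets a second spouse take the first spouse's arm. This correlates outcomes within arms and could push type I error upward. Neither simulation includes it.

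Finally, the 60% power levels might look like damage done by the unstratified test. They come from the 19.6% versus 17.5% conflict in 3.8. With the rates used in the formula, power is about 81-82% unstratified and 82-84% stratified.

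**Conclusion.** The point holds as a defect in the stated rule. Section 8.2 leaves the main estimate to chance imbalance and judgement, and in the expected case it omits the two factors used to stratify. The consequence is modest. From the strata effect alone, type I error is about 3.7-4.4% if the high stratum has 2 to 3.7 times the risk, and the power loss is about 0.3 to 4 points. Both shrink to nearly nothing if the strata are weakly prognostic.

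These sizes rest on assumed stratum risks, stratum shares and center differences. They compare tests of proportions rather than the life-table or log-rank methods that the trial would use. The documents do not support a claim of inflated type I error under the rule as written, of net conservatism, or of a primary analysis that expressly excludes the strata. The case for change is that the better rule costs almost nothing.

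**What to change.** Replace the conditional sentence in 8.2 with one pre-specified primary comparison that accounts for Clinical Center and the two 2-hour-glucose strata whatever the observed balance. One suitable form is a stratified log-rank test, with a Cox model stratified by the same factors for the estimate. State in advance how small centers are pooled, name any further covariates beforehand, and describe the baseline tables as descriptive only.

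When writing this, say how second spouses are handled, since they are not allocated from the randomization list.

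As a secondary point, state in 8.3.2 that each continuous variable is analysed with adjustment for its own baseline value. The present wording does not exclude this.

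The cost is wording only: no extra subjects, visits or measurements.
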